#### Secondary Analyses

Analysis for continuous clinical outcomes will be conducted via an ANCOVA to compare change values between study groups, adjusted for baseline values and patient population (ie, patients with chronic kidney disease, hepatology, and kidney and liver posttransplant). No imputation of missing values will occur.

Supplementary descriptive analysis of participant technology choices and patient-led goal attainment will be conducted. Summative statistics for the proportion of engagement among participants in the intervention arm will be collected and analyzed postintervention. A significance level of *P*<.05 will be used for all analyses.

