Advances in health technology have provided new opportunities to assist lifestyle interventions and improve the management of the MetS [13,17]. Asynchronous (eg, online information and resources) and synchronous (eg, telehealth appointments with health professionals) technology interventions have emerged as viable options for delivery of health care. These have the potential to address current barriers to service delivery, particularly in rural areas, including continuity of care, availability of resources, and location of services [25]. A range of factors within complex tertiary care systems, including patient-related factors (eg, values, goals, motivations, skills, and knowledge), organizational-related factors (eg, culture, priorities, and structural systems), and external factors (eg, health care funding), must be considered when assessing the feasibility of disruptive service change [26]. Patient-led approaches allow for the patient’s perspective to be considered when receiving health care [27]. These approaches ideally assist patients in individualizing their self-management plans through selecting which services they want to engage with and through what means.

This study will expand on the current literature by testing the implementation of a health technology–assisted lifestyle intervention for people with complex chronic disease. The primary aim will be to test the feasibility of this intervention, determined by safety, recruitment rate, retention, exposure uptake, and telehealth adherence. The secondary aims include assessing the clinical effectiveness of the intervention, (including metabolic syndrome severity, dietary quality, physical activity and sedentary behavior, exercise capacity, neuromuscular fitness, muscular pain, clinical parameters, quality of life, perceived confidence, fatigue, and sleep quality and quantity), patient-led goal attainment, treatment fidelity, exposure demand, and participant perceptions. We hypothesize that delivery of lifestyle interventions using health technology is feasible, can address the barriers to service delivery, and will demonstrate improved clinical outcomes over standard care.

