### Randomization and Allocation

Participants will be randomized 1:1 to the intervention group (group 1) or to a control group (group 2) that will receive standard care and individualized dietetic advice to support improvements in diet quality [28]. Computer-generated randomization will be completed using the REDCap research management system [29]. Groups will be stratified by referral source: (1) chronic kidney disease clinic, (2) hepatology clinic, or (3) liver or kidney posttransplant clinic. Participants will be informed of their group allocation following baseline assessment by the research project officer.

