### Statistical Analysis

#### Sample Size

As this will be a feasibility study, a sample size calculation was not performed for the primary outcome. To allow for reliable findings, the sample size calculation was conducted using the MetSSS for clinical effectiveness as a secondary outcome. Assuming a correlation of 0.5 between baseline and 26-week MetSSS and an effect size of 0.42 (representing a change of 0.8 in the intervention group and no change in the control group, with a pooled standard deviation of 1.9), the Stata procedure “sampsi” suggests that 67 participants per arm will be required to achieve 80% power to detect a significant difference at the 5% level (2-sided) using an analysis of covariance (ANCOVA). Allowing for 20% dropout, the required number of participants to be recruited will be 168 (84 per arm).

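### The clinical effectiveness hypothesis names no deciding outcome, and about 29 measures are all tested at 5% although only MetSSS sizes the trial

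*Protocol article*

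**What the plan says.** The last sentence of the Introduction states a hypothesis in three parts, the last being that the intervention "will demonstrate improved clinical outcomes over standard care". It does not specify the outcome.

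Under Sample Size, no calculation is made for the feasibility outcome. Instead, "the sample size calculation was conducted using the MetSSS for clinical effectiveness as a secondary outcome". The inputs are given as follows: "Assuming a correlation of 0.5 between baseline and 26-week MetSSS and an effect size of 0.42", the latter representing "a change of 0.8 in the intervention group and no change in the control group, with a pooled standard deviation of 1.9". This leads to 67 evaluable participants per arm for 80% power at two-sided 5%, and to 168 recruited.

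Under Secondary Analyses, continuous clinical outcomes are compared between arms by ANCOVA on change, adjusted for baseline and patient population. The section closes with "A significance level of *P*<.05 will be used for all analyses". MetSSS is not mentioned there. It comes first among the clinical effectiveness outcomes in Table 2 and under Secondary Outcomes, but is not called the main or key one.

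Under Primary Outcome and Primary Analysis, feasibility is judged by safety plus three of four fixed thresholds. Safety is judged by a chi-square test on study-related serious adverse events.

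**The concern.** The hypothesis is directional and the trial is powered on a clinical outcome, so the clinical comparisons are more than description. As written, a significant result on any one food group, activity score, strength test or questionnaire could be cited in support of the hypothesis on the same footing as MetSSS. A null MetSSS result could be set aside for another outcome without departing from the text. The error rate of the effectiveness claim is then that of the whole set of tests, not the 5% used in the sample size calculation.

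**Working it through.** **1. The plan's own figure.** Inputs from Sample Size: difference 0.8, SD 1.9, baseline to follow-up correlation 0.5, two-sided 5%, 80% power, 20% dropout.
- Standardised effect: 0.8/1.9 = 0.42.
- ANCOVA residual SD: 1.9 × √(1 − 0.5²) = 1.645.
- n per arm = 2 × (1.960 + 0.842)² × 1.645²/0.8² = 66.4, rounded up to 67.
- With dropout: 67/(1 − 0.20) = 83.75, rounded up to 84 per arm, 168 in total.

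The figure reproduces. Power at 67 per arm is 80.3%.

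**2. Count of named quantitative clinical measures** (Table 2 and the sections under Clinical Effectiveness).

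| Domain | Measures |
|---|---|
| MetSSS | 1 |
| Diet: six food groups, fibre, unsaturated oils, discretionary foods | 9 |
| Activity: four IPAQ-SF scores, one wearable measure | 5 |
| 6-Minute Walk Test | 1 |
| Single chair stand, five chair stands, grip in each hand | 4 |
| Pain 1, quality of life 1, self-efficacy 2, fatigue 1 | 5 |
| Sleep: PSQI, wearable total | 2 |
| Resting heart rate, BMI | 2 |
| **Total** | **29** |

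The count leaves out the serum analytes, whose appendix is not shown. It also leaves out goal attainment, which is compared between groups under Goal Attainment Score but called descriptive under Secondary Analyses. Counting only the headline rows of Table 2 gives about 11 to 15.

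**3. Chance of at least one significant result favouring the intervention, with no true effects.** Each two-sided 5% test has a 2.5% chance of a significant result in that direction.
- Independent tests: 1 − 0.975^m. For m = 29 this is 0.52, for m = 15 it is 0.32, and for m = 11 it is 0.24.
- Equal correlation ρ between test statistics: 1 − ∫ φ(u) Φ[(1.960 − √ρ·u)/√(1 − ρ)]^m du. The article gives no correlations between outcomes, so ρ is an assumption shown as a range.

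| m | ρ = 0 | 0.1 | 0.2 | 0.3 | 0.5 |
|---|---|---|---|---|---|
| 29 | 52% | 45% | 40% | 34% | 25% |
| 15 | 32% | 29% | 26% | 23% | 18% |
| 11 | 24% | 23% | 21% | 19% | 15% |

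At m = 30 the figures are 53% if independent and 46% down to 25% over the same correlations, so one measure more or less hardly matters.

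**4. Either direction, for comparison.** 1 − 0.95^29 = 0.77. This includes results favouring control, which cannot support a hypothesis of improvement.

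**5. Effect of the remedy.** With MetSSS as the only deciding test, the chance of a false claim of benefit is 2.5%, and 67 evaluable per arm still gives 80%. A Bonferroni correction over 29 tests would use 0.05/29 = 0.0017 (critical value 3.134). The expected MetSSS statistic is 0.8/(1.645 × √(2/67)) = 2.814, so power would be Φ(2.814 − 3.134) = 37%. The n needed would be 2 × (3.134 + 0.842)² × 1.645²/0.8² = 133.7, or 134 per arm.

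**The case against.** The strongest reply is that this is a feasibility trial. No secondary P value enters the feasibility rule, and unadjusted secondary outcomes are ordinary in such trials. That stands as far as feasibility is concerned. It does not cover the separate hypothesis of clinical improvement, which the plan states, powers and tests.

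A second reply is that MetSSS already leads in practice, since it is listed first and sizes the trial. This is fair, and it makes the remedy a small one. But the analysis text does not carry that role through.

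A third is that multiplicity is commonly left to the analysis plan, which is not shown. The mere absence of an adjustment would indeed be no finding. The point here is narrower: the article sets one threshold for all analyses and leaves its own hypothesis without a deciding outcome. A separate plan could still add a hierarchy or exploratory labels.

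A fourth is that the count is one reading. The article gives no scoring for the pain questionnaire, and self-efficacy uses four-point Likert scales, so ANCOVA may not apply to these three measures. Without them, 26 independent tests give 1 − 0.975^26 = 48%.

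A reader might infer that the hypothesis would probably be supported by chance, citing 77%. The documents do not support this. That figure counts both directions. The favourable chance passes one half only with at least 28 independent tests, and many of these measures share a domain or an instrument. Nor does the article say that any single positive result will be used to claim effectiveness. It only leaves that open.

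**Conclusion.** The point holds as a gap between the stated hypothesis, the powered outcome and the testing rule. With no true effects, the chance of at least one significant result in the intervention's favour is about 52% for 29 independent tests and about 25% to 45% at equal correlations of 0.5 to 0.1. That is roughly 10 to 21 times the 2.5% of a single test. On the narrow count of 11 to 15 outcomes it is about 15% to 32%.

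These figures rest on the count, on assumed correlations and on no outcome having a true effect. The unlisted analytes would raise them, and stronger correlation would lower them. The feasibility conclusion does not depend on any of this. The change is a cheap improvement to the wording, not the repair of an invalid design.

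**What to change.** - **Introduction:** tie the effectiveness part of the hypothesis to the between-arm difference in MetSSS at 26 weeks.
- **Secondary Analyses:** name that difference, by the ANCOVA already specified and at two-sided 5%, as the single key clinical outcome. State that the other clinical outcomes are exploratory, reported as estimates with 95% confidence intervals, and do not on their own support a claim of effectiveness.
- **Significance level:** limit the change to the clinical outcomes. The sentence on the 5% level also covers the chi-square safety comparison under Primary Analysis, and deleting it outright would leave that test without a stated level.

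The cost is a few sentences. The sample size stays at 168 and MetSSS power at 80%. The downside is that a striking result on another clinical outcome can be reported and discussed, but cannot carry the effectiveness claim.

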#### Patient and Public Involvement

Significant consumer engagement was undertaken in the design of the research question and health priorities; this involved focus groups and interviews [21,24,49,52,53]. This informed the design of the intervention, particularly the inclusion of patient choice in how to engage with technology and the acceptability of using telehealth options for diet and exercise support. Patients were not involved in the recruitment or conduct of the study and did not assess the burden of the intervention. Written summaries of the results will be sent to participants upon completion of the study.

#### Ethics Approval

This trial has been approved by the Metro South Human Research Ethics Committee (HREC/2019/QMS/58285) and The University of Queensland Human Research Ethics Committee (2020000127). The trial adheres to the Helsinki declaration and has been prospectively registered with the Australian New Zealand Clinical Trial Registry (ACTRN12620001282976).

## Results

The study was funded in 2019 and has been approved by the Metro South Human Research Ethics Committee and The University of Queensland Human Research Ethics Committee. Due to the COVID-19 pandemic, study enrollment was delayed for 6 months. Participant enrollment has commenced and will continue through June 2022. End-of-program assessments will continue through December 2022, when data collection is expected to be completed. Analysis, interpretation, and preliminary dissemination of results are planned for January 2023 to June 2023 through scientific conferences. The main results are expected to be published by August 2023.

## Discussion

This trial will test the implementation of a technology-assisted lifestyle intervention for a diverse group of patients with complex chronic conditions who receive specialist outpatient care from the tertiary health system. While telehealth delivery of dietary interventions has been shown to be cost-effective in research settings [54], this mixed methods approach incorporates feasibility and effectiveness outcomes, as well as patient engagement strategies to evaluate service redesign in a real-world clinical setting. While trials of technology such as telephone coaching or video-enabled telehealth counselling sessions have generally been deemed feasible for some complex conditions [13,48], patients’ desire for greater choice and to lead decision-making around engagement with a diverse suite of technologies is clear [21,52]. We expect that the intervention will be able to address a number of barriers to engaging with lifestyle interventions in the hospital and health care system, and that it will allow improved access to specialist care compared to standard practice. The results of this project will be of interest to researchers and policy makers who are strategically investing in a transition to telehealth models of care. This is especially pertinent in the context of the global COVID-19 pandemic, which challenged traditional health care delivery models. Patient-led health technology approaches to lifestyle intervention may be instrumental to the future of health service design. Recruitment in this study will be limited to patients referred to dietetic services as part of their usual tertiary hospital outpatient care, and results may thus lack generalizability to other settings. The results will be broadly disseminated (locally, nationally and internationally) through established networks of the investigator team. There will be no restrictions placed on publication of any results. There is no intention for the use of professional writers. All authors will meet journal requirements for authorship.

## Appendix

Multimedia Appendix 1 Biochemical analytes.

Multimedia Appendix 2 Detailed description of telehealth exercise intervention.

## Abbreviations

5xSTS: repeated chair stand test
6MWT: 6-Minute Walk Test
AEP: accredited exercise physiologist
ANCOVA: analysis of covariance
APD: accredited practicing dietitian
DASH: dietary approaches to stop hypertension
FACIT: Functional Assessment of Chronic Illness Fatigue
HR: heart rate
HRR: heart rate reserve
IPAQ-SF: International Physical Activity Questionnaire Short Form
MET: metabolic equivalent
MetS: metabolic syndrome
MetSSS: Metabolic Syndrome Severity Score
MNMQ: Modified Nordic Musculoskeletal Questionnaire
PSQI: Pittsburgh Sleep Quality Index
RiR: repetitions in reserve
SAE: serious adverse event
SMART: specific, measurable, achievable, realistic, timely
